# A Technological-Based Platform for Risk Assessment, Detection, and Prevention of Falls Among Home-Dwelling Older Adults: Protocol for a Quasi-Experimental Study

**DOI:** 10.2196/25781

**Published:** 2021-08-12

**Keywords:** fall prevention, technological platform, elderly, Otago Exercise Program

## Abstract

**Background:**

According to the United Nations, it is estimated that by 2050, the number of people aged 80 years and older will have increased by 3 times. Increased longevity is often accompanied by structural and functional changes that occur throughout an individual’s lifespan. These changes are often aggravated by chronic comorbidities, adopted behaviors or lifestyles, and environmental exposure, among other factors. Some of the related outcomes are loss of muscle strength, decreased balance control, and mobility impairments, which are strongly associated with the occurrence of falls in the elderly. Despite the continued undervaluation of the importance of knowledge on fall prevention among the elderly population by primary care health professionals, several evidence-based (single or multifaceted) fall prevention programs such as the Otago Exercise Program (OEP) have demonstrated a significant reduction in the risk of falls and fall-related injuries in the elderly within community settings. Recent studies have strived to integrate technology into physical exercise programs, which is effective for adherence and overcoming barriers to exercise, as well as improving physical functioning.

**Objective:**

This study aims to assess the impact of the OEP on the functionality of home-dwelling elderly using a common technological platform. Particularly, the impact on muscle strength, balance, mobility, risk of falling, the perception of fear of falling, and the perception of the elderly regarding the ease of use of technology are being examined in this study.

**Methods:**

A quasi-experimental study (before and after; single group) will be conducted with male and female participants aged 65 years or older living at home in the district of Porto. Participants will be recruited through the network COLABORAR, with a minimum of 30 participants meeting the study inclusion and exclusion criteria. All participants will sign informed consent forms. The data collection instrument consists of sociodemographic and clinical variables (self-reported), functional evaluation variables, and environmental risk variables. The data collection tool integrates primary and secondary outcome variables. The primary outcome is gait (timed-up and go test; normal step). The secondary outcome variables are lower limb strength and muscle resistance (30-second chair stand test), balance (4-stage balance test), frequency of falls, functional capacity (Lawton and Brody - Portuguese version), fear of falling (Falls Efficacy Scale International - Portuguese version), usability of the technology (System Usability Scale - Portuguese version), and environmental risk variables (home fall prevention checklist for older adults). Technological solutions, such as the FallSensing Home application and Kallisto wearable device, will be used, which will allow the detection and prevention of falls. The intervention is characterized by conducting the OEP through a common technological platform 3 times a week for 8 weeks. Throughout these weeks, the participants will be followed up in person or by telephone contact by the rehabilitation nurse. Considering the COVID-19 outbreak, all guidelines from the National Health Service will be followed. The project was funded by InnoStars, in collaboration with the Local EIT Health Regional Innovation Scheme Hub of the University of Porto.

**Results:**

This study was approved on October 9, 2020 by the Ethics Committee of Escola Superior de Enfermagem do Porto (ESEP). The recruitment process was meant to start in October, but due to the COVID-19 pandemic, it was suspended. We expect to restart the study by the beginning of the third quarter of 2021.

**Conclusions:**

The findings of this study protocol will contribute to the design and development of future robust studies for technological tests in a clinical context.

**Trial Registration:**

ISRCTN 15895163; https://www.isrctn.com/ISRCTN15895163

**International Registered Report Identifier (IRRID):**

PRR1-10.2196/25781

## Introduction

According to the United Nations, it is estimated that by 2050, the number of people aged 80 years and older will have increased by 3 times [1]. Increased longevity is often accompanied by structural and functional changes occurring throughout an individual’s lifespan and can be aggravated by certain behaviors, lifestyles, and environmental exposures, among other reasons. Some of the outcomes associated with these changes are loss of muscle strength, decreased balance control, and mobility impairments, which are risk factors strongly associated with the occurrence of falls in this population [2].

Globally, falls are highly prevalent in the elderly [3-5]. Although some asymmetries exist, it has been reported that about one-third of home-dwelling adults fall at least once a year, and of those who fall, two-thirds will experience another fall in the following year [4,6]. In this segment of the population, falls are complex events with multiple, dynamic interacting factors likely to lead to an increase in the frequency of such incidents with major implications on the quality of life [2]. The consequences of a fall can be extremely serious for the elderly and their families, as these falls can initiate or accelerate a vicious cycle of losses that can ultimately result in functional dependence leading to institutionalization [7,8]. Scientific research has identified several risk factors and has confirmed that the risk of falling increases with the number of existing risk factors [9]. Changes in gait and balance [2,9,10], decreased muscle strength [10], sensory deficits [2,10], functional decline [10], cognitive decline [2,9], musculoskeletal disease [4], neurological disease [2], endocrine or metabolic diseases [10], depression or depressive symptoms [9], urinary incontinence [10], the fear of falling [7,10], polymedication [2,9], and a history of a previous fall [2,4,9,10] are factors strongly associated with falls in the elderly. In a community context, research shows that the multifactorial web associated with these events also integrates risk factors present in household environments where the elderly perform their activities of daily living (ADLs) [11]; the synergistic and dynamic interaction of these risk factors with intrinsic factors increases the risk of falling.

Primary health care professionals should consider the existing evidence to develop interventions targeted at the elderly and their families [12] to identify and mitigate the environmental risks, and to promote safe behaviours. This intervention must include several programs effective for fall prevention, particularly when coupled with other approaches [9,11-13]. Changes in gait and balance are major factors associated with falls in the elderly, and rapid tests are recommended for the assessment of changes in gait and balance, such as the 30-second chair stand test (CST) [14], 4 stage balance test (4 SBT) [15], and timed-up and go test (TUGT) [9,16].

Despite the continued undervaluation of the importance of knowledge on fall prevention among the elderly population [11] by primary care health professionals, several fall prevention programs (single or multifaceted) have demonstrated a significant reduction in the risk of falls, number of falls, and fall-related injuries [6,9,13,17]. In fall prevention programs, an exercise component, either as a single intervention or integrated into multifaceted interventions, has proven effective in preventing these events and reducing associated injuries [6,9]. The Otago Exercise Program (OEP) developed at the University of Otago Medical School is an exercise program for fall prevention used in a community context internationally. The efficacy of the OEP has been attested in 4 randomized studies and 1 controlled multicenter study [6]. The focus of the OEP is to improve strength and balance with a simple, affordable, home-implemented, 12-month solution, which is monitored by a health professional through telephone interviews and home visits. The OEP was designed to be carried out autonomously by people in their homes, supported by a paper-based manual, after training with a physiotherapist for 4 individual sessions. Subsequently, other professional groups such as nurses have successfully administered the program [17,18].

Recent studies have strived to integrate technology into physical exercise programs that were revealed as effective for adherence and overcoming barriers to exercise, as well as for improvements in health and independence [19]. Currently, several technological solutions address specific aspects of the fall cycle; however, the majority of these do not address fall detection, fall risk assessment, and fall prevention simultaneously. The FRADE (Pervasive Platform for Fall Risk Assessment, Detection and Prevention) project seeks to develop a common technological platform that allows the integration of all these components. This platform consists of the use of sensors that will collect data and monitor the gait of the elderly. This platform can also send caregivers alerts and text messages in the event of a fall. The tablet application provides a set of fall prevention exercises based on the Otago Program; along with a wearable sensor, it allows for the monitoring of user performance and evaluation of progress. This study aims to assess the impact of an exercise program supported by a technological platform on functional variables associated with risk of falling and assess the ease of use of this technology by the elderly.

## Methods

### Study Design

A quasi-experimental study (before and after; single group) was carried out. Two research centres were involved in the project, the Nursing School of Porto (ESEP) and the Fraunhofer Portugal Assistive Information and Communication Solutions (AICOS).

### Recruitment and Sample

Participants aged 65 years or older who were living at home in the district of Porto, Portugal were recruited based on the following criteria.

The inclusion criteria are able to walk independently; cognitive impairment, as assessed by the Portuguese version of the Mini-Mental State Examination (cut-off points of 22 for 0-2 years of schooling, 24 for 3-6 years of schooling, and 27 for ≥7 years of schooling); no severe visual or hearing impairment; and willingness to participate in a physical exercise program with technological support.

The exclusion criteria are a self-reported chronic or acute illness for which exercise is contraindicated, history of hip or knee surgery or lower limb fracture in the last 12 months, current or previous participation in physical exercise programs in the last 6 months, and participation in another research study involving fall prevention programs.

After approval by the ESEP ethics committee, the recruitment of participants will start through the Living COLABORAR Network. This network is part of a Fraunhofer Portugal research center, and it participates in an organization of institutions that give social, health, and leisure support and promote the well-being of their clients, especially the elderly. Potential participants will be contacted by Fraunhofer researchers who will present the study objectives and collect information from people interested in participating in the study.

Subsequently, those willing to participate will be scheduled for an evaluation conducted at home by a rehabilitation nurse in 2 phases. The first phase involves screening potential participants based on the inclusion and exclusion criteria. Consequently, the questionnaire prepared for this study will be completed. These participants will spend a part of their days in the community center, where they will become familiar with the tablets.

The convenience sample will include at least 30 participants.

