### Informed Consent

Participation in the study is voluntary, and participants are free to withdraw from the study at any time. All participants will provide written informed consent before data collection begins in the first home visit. The benefits, risks, and guarantee of confidentiality during data collection and information security for the participants are all explained in the consent form, in addition to the detailed explanation provided by the rehabilitation nurses.

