### Intervention

The physical exercise program to be implemented is based on the OEP, including exercises aimed at improving balance, gait, and muscular strength in the lower limbs. The program is carried out by the elderly independently in their homes, supported by a paper-based manual, after in-person training with a health professional. In addition to the manual, the participants will have a common technological platform consisting of an Android tablet and a wearable sensor, which will enable them to access the OEP through interfaces with interactive feedback while exercising. This technological platform also allows interactive monitoring of the 5 strength exercises and 3 balance exercises (such as knee flexion, unipedal balance, and sit-and-stand).

In the first session at the participants’ homes, the rehabilitation nurse will train the participants to perform the exercises. Participants will be encouraged to carry out this program at least 3 times a week for 8 consecutive weeks. The rehabilitation nurse will provide participants with an in-person or telephone follow-up during these weeks.

The rehabilitation nurse will also instruct the elderly to wear comfortable clothes and shoes and inform the nurse if they experience joint or muscle pain. If such an event occurs, it is advisable to suspend the exercise.

Through the technological platform, the rehabilitation nurse will prescribe the OEP exercise plan for each participant, defining the exercises to be performed and the appropriate level of each exercise along with the frequency.

Each exercise session will have 3 sequential phases: warm-up phase, main phase, and relaxation phase with stretching exercises, which is a return to the calm phase. The progression in the exercises will be guided by the rehabilitation nurse and will be adapted to the functional capacity of the elderly. Regarding the intensity of the exercises, these will be performed without weights.

The OEP exercises and phases are explained in Multimedia Appendix 1. Throughout the duration of the program, participants will be followed up in person and by telephone by the rehabilitation nurse according to the intervention schedule (Figure 1).

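### The inclusion list makes cognitive impairment on the MMSE a condition of entry, contradicting the stated population and procedures that presume intact cognition

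*Protocol article*

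**What the plan says.** The Recruitment and Sample section of the protocol article opens its inclusion list with independent walking and gives as the second item "cognitive impairment, as assessed by the Portuguese version of the Mini-Mental State Examination". In parentheses it gives "cut-off points of 22 for 0-2 years of schooling, 24 for 3-6 years of schooling, and 27 for ≥7 years of schooling". The next item reads "no severe visual or hearing impairment", and the last is willingness to take part in technology-supported exercise.

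The exclusion list begins "The exclusion criteria are a self-reported chronic or acute illness for which exercise is contraindicated". It continues with recent hip or knee surgery or lower limb fracture, current or recent exercise programmes, and participation in other fall-prevention research. Cognition is not among its items.

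The abstract's Objective describes the population without reference to cognition: "This study aims to assess the impact of the OEP on the functionality of home-dwelling elderly using a common technological platform". On conduct, the Informed Consent section says "All participants will provide written informed consent before data collection begins in the first home visit", and the Intervention section says "The program is carried out by the elderly independently in their homes, supported by a paper-based manual", after training by a health professional.

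**The concern.** An inclusion criterion is a condition that a volunteer must meet. As printed, this one requires a finding of cognitive impairment. The same section says that a rehabilitation nurse screens volunteers against these criteria, so the sentence is an operative rule and not background.

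What is at stake is which population the trial describes. If the rule is followed to the letter, the sample is a cognitively impaired group that the title, objective and aim never mention. If staff assume the opposite, the published criterion does not describe the people enrolled. In both cases a reader cannot tell to whom the Timed Up and Go (TUGT), FES-I and SUS results apply. The usability result is the most exposed, because ease of use by older people is a stated aim and cognition plausibly affects it.

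**Working it through.** No arithmetic applies; the check is a comparison of texts.

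**1. Can a negation be read into the item?** The inclusion list has four items separated by semicolons: independent walking, cognitive impairment by MMSE, no severe sensory impairment, and willingness. The sensory item carries its own *no*, which stands after the cognitive item and does not govern it. Nothing before the cognitive item negates it either.

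**2. Do the cut-offs settle the direction?** They give 22, 24 or 27 according to schooling, with no *above*, *below* or *at or below*. Take a volunteer with 5 years of schooling, whose cut-off is 24:

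| Reading | Eligible | Ineligible | Score of exactly 24 |
|---|---|---|---|
| As printed (impairment required) | impaired side of 24 | intact side of 24 | not stated |
| Negation supplied (impairment absent) | intact side of 24 | impaired side of 24 | not stated |

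The two eligible sets are complements: nobody qualifies under both readings. The cut-offs cannot decide between them, and a score equal to the cut-off is unclassified under either.

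**3. Does the exclusion list correct it?** It has four items, and none concerns cognition.

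**4. Does any other section describe an impaired population?** The title, the abstract's Objective and Methods, and the aim at the end of the Introduction refer to older adults living at home, with no cognitive qualifier. The Introduction mentions cognitive decline once, as one of many risk factors for falls.

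**5. Do the procedures fit a sample selected for impairment?**
- Informed Consent: participants sign for themselves.
- Intervention and Technological Platform: after nurse training, participants exercise at home, select a weekly plan on a tablet and wear sensors. The nurse prescribes the exercises, guides progression and follows up in person or by telephone.
- Fear of Falling and Technology Usability: FES-I and SUS rest on the participant's own answers.
- Discussion: the limitations cover the nonrandom sample, the lack of a control group, technological literacy and sessions done alone. Cognitive impairment is absent, although it would be an obvious limitation if it were required for entry.

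Steps 1 to 3 show that the printed rule requires impairment and that nothing reverses it. Steps 4 and 5 show that the rest of the article is written for a different population.

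**The case against.** The strongest reply is that this is a dropped word. The neighbouring sensory criterion is phrased as an absence, the rest of the plan presumes intact cognition, and a journal article condenses a fuller protocol that may well carry the negation. As an explanation this is probably right, and it rules out one stronger inference: that the sponsor means to enrol people with impaired cognition. The documents show a contradiction in the wording, not that intention. It does not remove the defect, because the article states the rule outright. This is a wrong statement, not a detail left to another document.

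Other inferences a reader might draw also go too far:
- **That participants exercise unsupervised.** Nurses train them at home and follow them throughout, and the Discussion says that only some sessions are done alone.
- **That the outcomes are self-reported.** The primary outcome, TUGT, is a timed test assessed by a nurse. The article labels the sociodemographic and clinical variables as self-reported. It does not say how falls are counted, and the platform includes a fall detector.
- **That consent is defective because no proxy is described.** Capacity and proxy procedures may sit in the full protocol, and the article does not equate an MMSE result with incapacity. The consent text shows only that capacity is presumed.
- **That all of the 30 or more participants will be impaired.** This restates the literal rule; it does not predict what screening staff will do.
- **That no one has yet been enrolled.** The Results say that recruitment was suspended and that the study would restart, while Study Design and part of Recruitment and Sample use the past tense. The status is not clear enough to rely on.

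**Conclusion.** Wrong as written. The published rule requires cognitive impairment by MMSE for entry. No other text negates it, and it conflicts with the article's own population and procedures. The effect is one of kind: the literal rule admits the complement of the group that the negated rule would admit, so it bears on every participant and not on borderline scores alone. The missing direction and the unclassified boundary score are a smaller, separate gap in the same sentence.

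The conclusion rests on the article's text alone. That a negation was omitted is the likeliest explanation but remains an assumption, which only the ethics-approved protocol can confirm.

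**What to change.** Before recruitment restarts, compare the criterion with the ethics-approved protocol and correct the article to match the intended rule:
- If intact cognition is intended, restate the criterion as absence of cognitive impairment on the Portuguese MMSE, or move impairment to the exclusion list.
- State which side of 22, 24 and 27 counts as impaired, and how a score equal to the cut-off is classed. The article does not supply this, so it should come from the approved protocol.
- If impairment is truly required, say so in the objective and target population, and revise the consent and self-report procedures accordingly.
- If anyone was screened before the suspension, establish which rule was applied and report it.

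In the first case the cost is a one-line correction, with no change to the sample size, outcomes or analysis. In the second it is a substantive revision of the protocol.

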### Setting

This study will be deployed in the city of Porto, within the area of Bonfim at the council in which the care center is located. The population of Bonfim is about 24,265 people, of which 27.1% are elders (>65 years old), according to the 2011 census. This day center is located in an area of the city with an aging population, in which people aged 65 years and over represent 36.3% of the population and young people represent 18.2% of the population, with a total dependency index of 54.9%.

The elderly institution has 2 modalities: long-term hospitalization (for very dependent people) and a community center. The participants for this intervention will only be enrolled from the elderly who attend the activities in the community center but live in their own homes. The intervention will take place in the houses of the participants.

